### Sample size calculation

Based on a clinical meaningful effect size of 10 points on the FSMC scale between baseline (D0) and the primary follow-up (Day 11) measurements, and assuming a standard deviation of 12.5 (20, 21, 108), the estimated sample size is 25 per arm and 50 participants in total. This will yield 80 % power of reaching evidence of a treatment effect, with a *p*-value under 0.05. Accounting for a drop-out of 15%, our final sample size is 29 per arm, 58 in total.

### Recruitment procedure

Eligible patients will be identified by clinicians at the outpatient clinic at the Danish Multiple Sclerosis Centre, Copenhagen University Hospital - Rigshospitalet Glostrup. They will be provided with written information at least 24 h prior to enrolment and oral information about the study purpose and methods, prior to inclusion. To facilitate recruitment, there will be regular meetings across the 2 centers, and promotional talks to clinical (non-research) staff at the recruiting site. Additionally, flyers and recruitment material will be available for sharing across patient-networks and via the Danish Multiple Sclerosis Society (Scleroseforeningen).

## Methods: assignment of intervention

### Allocation and sequence generation

Participants will be randomly assigned (1:1) to the intervention or sham arm using a computer-generated sequence via block-randomization with variable block sizes (2, 4, or 6 participants) to ensure balanced group sizes and minimize allocation predictability. This approach controls for potential bias related to evolving staff expertise over time. The sequence is generated using MatLab (The MathWorks Inc., Natick, MA, United States) with a length of at least 70 to account for potential dropouts. Randomization was performed by author VW, who is not involved in intervention delivery or outcome assessment. All other personnel are blinded to the treatment status.

### Allocation concealment and implementation

Allocation concealment will be maintained using sealed, opaque envelopes opened only on the first intervention day. Each participant receives a unique 6-digit code which will be distinct from the subject ID used for data management. The code will be entered into the stimulator prior to each session and does not disclose group allocation. The randomization key, containing block order and treatment assignment, will be securely stored and inaccessible to investigators involved in intervention delivery until trial completion.

Participants will be recruited and enrolled by an investigator not involved in sequence generating and envelope preparation. Participants will have completed all baseline behavioral and 7T MRI assessments prior to group assignment. Envelopes will be opened before baseline TMS measurements, on the first intervention day.

### Blinding

Allocation blinding is maintained through the integrated design of the coil and stimulator. The coil provides no visual cues regarding its active or sham side and automatically detects its orientation via an internal sensor. The sham side is engineered to replicate the auditory and tactile peripheral co-stimulation created by active stimulation. The stimulator displays no indication of condition assignment. To preserve blinding between consecutive participants, the coil is removed and reattached for each session.

To mimic the cutaneous sensation associated with active TMS pulses and preserve blinding, all participants, regardless of group allocation, will receive low-intensity electrical stimulation to the forehead, positioned as close as possible to the stimulation site while respecting the individual’s hairline. This electrical stimulation is a built-in feature of the B65-Cool-A/P coil and MagPro XP Orange Edition stimulator.

The electrical stimulation intensity will be automatically adjusted by the stimulator to match the sensation produced by the magnetic coil, using a fixed scaling factor. This factor will be applied uniformly across all participants to standardize the sensory experience and minimize the risk of unblinding for both participants and intervention administrators. Internal pilot testing with TMS-experienced individuals confirmed that this setup provides a credible sham condition. Success of blinding will be assessed by asking each participant to indicate which group allocation they received, as part of the TMSens questionnaire (105).

Emergency unblinding requests will be evaluated individually. If necessary, unblinding will involve simulating a session and manually verifying the treatment condition based on device output.

## Methods: data collection, management and analysis

### Data collection methods and management

#### Data collection

##### Questionnaires

Questionnaire data are collected and managed using REDCap (Vanderbilt University, TN, United States), a secure, web-based software platform designed to support data capture for research studies, hosted at the Capital Region of Denmark (RegionH) (109, 110). Access to REDCap is granted through an electronic tablet (Apple, California, United States) for visits, and by an electronic link to the participants’ emails for at-home questionnaires.

##### MRI/MRS data acquisition

Across the three scan sessions, the scans take place in the same order: Scouts + calibration scans; MPRAGE for MRS planning; MRS; Structural 1; rs-fMRI; DTI; other structural scans. The specific aim is to always have equal gradient history for the MRS, as this may affect and bias the results (111). All MRI scans are quality-checked immediately after acquisition by trained staff and repeated if of poor quality. All imaging parameters are detailed in Supplementary Table S2.

^1^H-MRS will be acquired with a semi-localized by adiabatic selective refocusing (sLASER) sequence with a voxel 20 mm cubic, as in (112). Voxel placement will be done on a T1-weighted MPRAGE image, acquired immediately prior to the sLASER scan. MRS is performed at 3 voxel positions per session: Bilateral M1 hand knob (113), covering also the PMd; and a midline parietal voxel, corresponding to the inferior portion of the precuneus. Voxel placement will be aided by SmartBrain™ (Philips, Best, Netherlands) and manually corrected.

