**Methods:**

This randomized, double-blinded, sham-controlled, parallel-group trial investigates the efficacy of premotor TMS in treating fatigue in MS. Fifty-eight patients with MS will receive either active or sham TMS targeting the left dorsal premotor cortex (PMd). On five consecutive days, participants will undergo 30-min sessions using a novel low-frequency (0.72 Hz) paired-pulse repetitive TMS protocol with an interstimulus interval of 33 ms. The primary endpoint is the change in FSMC score 6 days post-intervention. Secondary outcomes include additional fatigue assessments and quantification of regional γ-aminobutyric acid (GABA) and glutamate concentrations of the targeted PMd, via ultra-high-field (7T) magnetic resonance spectroscopy. We hypothesize that active treatment will result in greater fatigue reduction than sham treatment and correlate positively with an increase in regional GABA in the stimulated premotor region. Exploratory endpoints include structural and functional connectivity changes assessed with 7T resonance imaging and motor cortical excitability changes measured with TMS.

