The stimulation target, the left PMd, is defined in montreal neurological institute (MNI) space (60) at x, y, z-coordinates (34, −2, 66), based on prior findings (21). This target is transformed into subject-specific space using individual T1-weighted and T2-weighted MRI brain scans. The optimal coil position will be calculated with SIMNIBS software (version 4.5^1^) as the scalp position inducing the largest mean electric field in the target region (61). Individual T1w and T2w MRI images will be segmented to a SIMNIBS compatible mesh using CHARM (62). The induced e-field for the B65-Cool coil (63) will be calculated (64, 65) in a 20 mm search radius at 1 mm resolution, with 40-50-degrees of rotation from the mid-sagittal plane, with an angular resolution of 1 degree.

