### Secondary outcome

#### 7 tesla proton magnetic resonance spectroscopy (^1^H-MRS)

The main secondary outcome is the between-group difference in changes in regional neurometabolite concentrations, specifically GABA and Glu, in the targeted left PMd, from baseline to the short-term follow-up on the final day of the intervention (Day 5). These concentrations will be assessed using ^1^H-MRS, acquired from a voxel positioned to cover the left PMd/M1 region. To assess neurometabolic network-level effects, an additional ^1^H-MRS voxel will be acquired in the contralateral (right) PMd/M1 region, to evaluate remote transhemispheric modulation. A voxel placed in the midline parietal region, will serve as a control site not expected to respond to the intervention. In addition to the short-term (Day 5) effects, longer-term effects will also be assessed at the primary follow-up 6 days post-intervention (Day 11), together with clinical outcome measures.

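### The main secondary outcome is worded as metabolite change in the stimulated left PMd but measured in one voxel that pools PMd with M1, so a change cannot by itself be attributed to PMd

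*Protocol article*

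**What the plan says.** The protocol article describes the region of the main secondary outcome in several ways.

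- **Abstract, Methods.** Active treatment is expected to "correlate positively with an increase in regional GABA in the stimulated premotor region".
- **Secondary outcome (7 tesla MRS).** The first sentence defines the outcome as change in metabolites, "specifically GABA and Glu, in the targeted left PMd, from baseline to the short-term follow-up". The next says that the signal is "acquired from a voxel positioned to cover the left PMd/M1 region".
- **MRI/MRS data acquisition.** The sequence is run "with a voxel 20 mm cubic", at three positions: "Bilateral M1 hand knob (113), covering also the PMd; and a midline parietal voxel". On positioning: "Voxel placement will be aided by SmartBrain™ (Philips, Best, Netherlands) and manually corrected".
- **Intervention—rTMS.** The stimulation target is a fixed MNI coordinate, (34, −2, 66), carried into each participant's own anatomy. "The optimal coil position will be calculated with SIMNIBS software".
- **Objectives.** The secondary objective concerns the motor and the premotor cortex together.
- **Discussion.** The stimulation protocol is said to suppress activity at the PMd itself and in motor regions connected to it.

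**The concern.** The outcome label is narrower than the measurement. Two sentences promise a result at the stimulated premotor site. The data will be a single value from a cube set on an M1 landmark and stated to include PMd.

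This matters because the outcome is the trial's mechanistic test: does stimulating PMd shift the balance towards inhibition, and does that shift track fatigue relief? With the label as it stands, a rise in GABA that arose in M1 could be reported as a local premotor effect. A null result could be read as no local effect without anyone knowing how much of the stimulated spot was sampled.

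**Working it through.** The plan gives no figure to reproduce on this point, so the check compares the passages and adds a short geometric illustration.

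**1. Label against measurement.**

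| Place in the article | Region named |
|---|---|
| Abstract, Methods | stimulated premotor region |
| Secondary outcome, first sentence | left PMd |
| Secondary outcome, second sentence | left PMd/M1 |
| MRI/MRS data acquisition | M1 hand knob, PMd also covered |
| Objectives | motor and premotor cortex |

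The first two rows are narrower than the other three.

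**2. Can the data separate the two areas?** Let w be the share of the left voxel's signal that comes from PMd and, for simplicity, let the rest come from M1. The measured change is

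Δ(voxel) = w × Δ(PMd) + (1 − w) × Δ(M1).

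That is one equation with two unknown changes and an unrecorded w. A positive Δ(voxel) fits a change in PMd only, in M1 only, or in both. The other two voxels (right PMd/M1 and midline parietal) add no equation for the left side. The Discussion expects Δ(M1) to be affected as well, so it cannot be set to zero. The between-arm difference in Δ(voxel) is still a valid randomised estimate of the effect on the weighted average.

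**3. Are voxel and target tied together?** The target comes from an MNI coordinate, with the coil position optimised in SimNIBS. The voxel comes from a hand-knob landmark on that session's MPRAGE, with software aid and manual correction. The article states no link between the two. The Simulated E-fields section plans post-hoc field simulation for quality control of the delivered dose and for predictors of treatment effect; it does not mention voxel coverage.

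**4. How far could coverage vary?** The half-width of the cube is 20/2 = 10 mm. Assume a spherical target of radius r whose centre lies d mm from the voxel centre along one axis of the cube. Neither r nor d is in the documents. The part outside is a cap of height h = r − (10 − d), limited to the range 0 to 2r, and

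share of target inside = 1 − h²(3r − h)/(4r³).

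Example: with r = 10 and d = 5, h = 5, so 1 − 25 × 25/4000 = 0.84.

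| d (mm) | r = 5 mm | r = 10 mm |
|---|---|---|
| 0 | 100% | 100% |
| 5 | 100% | 84% |
| 10 | 50% | 50% |
| 15 | 0% | 16% |
| 20 | 0% | 0% |
| 25 | 0% | 0% |

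A Monte Carlo calculation gave the same values. Coverage can be complete or absent, and the article does not say which applies.

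**5. Is baseline overlap free of treatment influence?** Allocation concealment and implementation states that baseline 7T MRI is finished before assignment. Overlap of the baseline voxel with the planned target is therefore a pre-randomisation variable.

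**The case against.** The strongest reply is that the article hides nothing. The outcome section calls the voxel PMd/M1 in its second sentence, the acquisition section says that PMd is covered, and the secondary objective already speaks of motor and premotor cortex. A pooled region also suits a mechanism that is expected to spread to motor areas. All of this stands. It makes the point one of attribution and labelling, not of an invalid measurement.

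A second reply is that a condensed article may leave voxel co-registration to the full protocol, the cited methods or the supplement. This also stands, so the absence of an overlap check is not itself counted as an error. The mismatch between the stated outcome and the stated voxel is on the page.

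A reader might infer three stronger things:

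- **That the voxel misses the target, so the trial can say nothing about the stimulated site.** The documents do not show this. They state that PMd is covered and give no distance that would contradict it.
- **That the effect will be diluted by a known fraction.** Any such fraction would be assumed, and it would require a purely local effect, which the Discussion does not expect.
- **That the right-hemisphere voxel has the same fault.** It does not. That voxel is labelled PMd/M1, serves to detect remote change and, as described, has no stimulation target to miss.

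**Conclusion.** The point holds as a mismatch between label and measurement with a real consequence for interpretation. In the Abstract and in the first sentence of the outcome definition, the region is PMd; the measured region is PMd plus M1. A change in that voxel cannot by itself be assigned to PMd rather than M1.

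The randomised comparison remains sound for the pooled region, and the primary outcome is untouched. The loss of specificity follows from the article's own text and needs no outside figure. Its size in any one participant is unknown: the coverage range of 100% to 0% rests wholly on assumed target radii of 5 and 10 mm and assumed offsets of 0 to 25 mm along one axis.

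**What to change.** 1. **Rename and limit.** Wherever the Abstract and the Secondary outcome section state the outcome, call it metabolite change in the *left PMd/M1 voxel*, in line with the Objectives, and confine the conclusion to that region.
2. **Reconcile the target first.** Intervention—rTMS calls the target left PMd but prints a positive x coordinate (34), which by the usual MNI convention lies in the right hemisphere. The text and the coordinate must be reconciled before any overlap is computed.
3. **Document coverage before unblinding.** Co-register the recorded baseline voxel to the participant's T1 image. Compute its overlap with the SimNIBS target and the voxel-mean simulated field, using the planned active coil position for every participant in both arms. Report both by arm.
4. **Use overlap sparingly.** Enter baseline overlap only as a continuous covariate or modifier in an analysis labelled exploratory. Do not repeat the main secondary analysis in a subset whose voxel contains the target: no threshold is defined, it would shrink a sample of 58, and using voxel positions from later sessions would select on post-randomisation scans.

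The cost is a narrower regional claim and some offline image processing. The inputs (T1 images, voxel positions, SimNIBS models) are already part of the planned work, so no new scans and no mid-trial change of voxel placement are needed.

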##### TMS

Single and paired-pulse TMS is performed pre- and post-intervention on intervention day one to capture changes in motor cortex excitation and inhibition. Experiment parameters are in accordance with safety guidelines (58). The cortical motor hotspot is defined as the corresponding scalp position at which TMS induces the largest and most consistent MEP in the first dorsal interosseus muscle (FDI). The location will be recorded and maintained using a stereotactic neuronavigation system for coil placement and continued control of correct coil position (Localite, Bonn, Germany) (114).

TMS stimulations will be delivered through a handheld B65 coil attached to a MagVenture X100 MagOption stimulator (MagVenture, Farum, Denmark). TMS-evoked EMG potentials are recorded with self-adhesive surface electrodes (Neuroline, Ambu, Ballerup, Denmark) attached to the right and left FDI muscle using a belly-to-tendon montage, with ground on right side ulnar styloid process. Electromyographic (EMG) signals will be sampled at 5 kHz, band-pass filtered (2–2,000 Hz) and amplified (500 times) using an eight-channel DC amplifier (D360, Digitimer, Hertfordshire, United Kingdom), digitized (Micro 1401-4 w/ ADC12, Cambridge Electronic Design, Cambridge, United Kingdom), and stored and displayed using Signal software version 8.0 (Cambridge Electronic Design, Cambridge, United Kingdom).

TMS pulses will be given every 4 s with 20% jitter when evoking MEPs in the relaxed target muscle. TMS during pre-contraction will use a lower ISI (3 s) to avoid fatigue. We will perform at least 15 trials per condition for recruitment-curves; 20 for paired-pulse experiments; and 21 (across bouts of 7, to avoid further fatigue) for ipsilateral silent period. More trials will be done if online data quality assessment deems this required for proper data quality. F- and M-waves will be evoked by supramaximal electrical stimulation of the right ulnar nerve (Digitimer DS7A, Digitimer, Cambridge, UK), their onsets latencies will be used to compute peripheral and central motor conduction times (104).

#### Data storage and management

All data entered will be kept in the electronical case report form REDCap and all MRI, EMG and accelerometer data will be stored on a secure server owned and operated by the DRCMR. Servers are regularly backed up by the IT-department of the Capital Region of Denmark, ensuring data integrity. All data, including data entered on REDCap, TMS and MRI data are reviewed during each session for quality and completeness. All data will be pre-processed between sessions. Missing data will be addressed at the last study visit. Data access will be limited to the study coordinator and sub-investigators involved in the study.

### Training of staff

#### Training prior to performing MRI experiments

All personnel involved in MRI procedures will have completed the department’s 7T-specific “MRI driver’s license” program, which includes comprehensive safety training according to current guidelines (115). During all scans, a medical doctor and a physicist will be available for assistance, if needed. There will always be at least two trained staff members present during the MRI scanning sessions.

#### Training prior to performing TMS experiments

All personnel involved in TMS and rTMS procedures will have completed the department’s “TMS driver’s license” program, which includes comprehensive safety training and supervised protocol-specific TMS sessions (41, 42). A dedicated TMS researcher with extensive expertise in EMG-based neurophysiology will be present for all Day 1 assessments to ensure high-quality data acquisition. All TMS and rTMS sessions will be conducted in the presence of a minimum of two trained staff members.

#### Statistical methods and analysis

All variables will be visually inspected for normal distribution through histograms and quantile-quantile plots prior to analysis and appropriately transformed if necessary. If data diverge from the normal distribution after transformation non-parametric testing will be performed. All tests will be 2-sided and statistical significance will be set at a *p*-value < 0.05. Data will be analyzed with R (116), Matlab (The MathWorks Inc., Natick, MA, United States) or similar software.

All data will be analyzed as a modified intention-to-treat, where all participants who have undergone at least one rTMS session (active or sham) and have follow-up data for outcomes will be analyzed according to the group they were randomized to. No per-protocol analyses are planned. The primary outcome will be analyzed as difference in change between baseline and clinical follow-up, between active and sham group. The statistical significance will be assessed with a mixed-effects linear model with the baseline as the reference. The primary analysis model will not adjust for depression, sleep, or physical activity measures, as the study is powered to detect overall treatment effects rather than covariate-adjusted effects. These variables will be examined in exploratory analyses as potential modifiers of treatment response, to assess whether treatment effects differ according to baseline levels or changes in these factors. Secondary outcomes with two timepoints (baseline and follow-up), will be compared as the difference in change between groups. Secondary outcomes with more timepoints will be analyzed with mixed-effects linear models with the baseline as reference. Neither the pre-registered primary or main secondary outcomes will be corrected for multiple comparisons, except where appropriate due to multiple measurements per participant. Exploratory analyses will be appropriately corrected for multiple comparisons prior to reporting.

There are no plans for predetermined subgroup analyses.

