### Eligibility criteria

Inclusion criteria: Participants must meet the following criteria to be eligible for the study: (i) Diagnosis of relapsing–remitting or secondary progressive MS, according to the 2017 McDonald criteria (52), (ii) Presence of moderate to severe fatigue, defined as a Fatigue Scale for Motor and Cognitive Functions (FSMC) score ≥ 53, and (iii) Age between 18 and 65 years.

Exclusion criteria: Participants will be excluded if they meet any of the following conditions: (i) Clinical relapse, corticosteroid treatment, or changes in MS-related medication within 3 months prior to inclusion, (ii) Moderate to severe depression, defined as a Major Depression Inventory (MDI) score ≥ 26 (53, 54) or other severe psychiatric, neurological, or somatic comorbidities, (iii) EDSS score (55) above 6.5 that would limit feasibility of 7T MRI, (iv) Contraindications to 7T MRI (56) or TMS (42, 44) in agreement with current safety guidelines (including pregnancy), (v) intake of pharmaceutical agents that may interfere with the neuromodulatory effect of rTMS, including tricyclic antidepressants (TCAs), monoamine oxidase inhibitors (MAOIs), GABAergic agents (benzodiazepines and gabapentin) and central stimulants such as modafinil. For feasibility reasons selective serotonin reuptake inhibitors (SSRIs), serotonin-norepinephrine reuptake inhibitors (SNRIs) are allowed. Use of selective serotonin receptor agonists (e.g., triptans for migraine) are allowed up to 48 h prior to intervention.

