### Primary outcome

The primary outcome of fatigue is measured as the difference in change in total FSMC (67, 68) score from baseline to follow-up at 6 days after the last rTMS intervention, between active and sham stimulation. Rating fatigue is largely subjective, and thus generally assessed as a patient-reported outcome (69, 70). However, the FSMC has the highest construct validity among often-used scales (69).

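### The inspect, transform, then go non-parametric rule is not confined to secondary outcomes, so the primary FSMC analysis and its scale are left to a visual judgement

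*Protocol article*

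**What the plan says.** All of the following is in the protocol article.

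- *Statistical methods and analysis* opens with a general rule: "All variables will be visually inspected for normal distribution through histograms and quantile-quantile plots prior to analysis and appropriately transformed if necessary". The next sentence gives the fallback: "If data diverge from the normal distribution after transformation non-parametric testing will be performed".
- The same section then gives the primary test: "The statistical significance will be assessed with a mixed-effects linear model with the baseline as the reference". It does not say that the general rule stops short of this outcome.
- *Primary outcome* puts the endpoint on the raw scale. It is "measured as the difference in change in total FSMC (67, 68) score from baseline to follow-up at 6 days after the last rTMS intervention", compared between active and sham.
- *Sample size calculation* is on that scale too: "Based on a clinical meaningful effect size of 10 points on the FSMC scale", "assuming a standard deviation of 12.5", giving 25 per arm.

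The section names no transformation and no non-parametric test. It gives no criterion for divergence beyond the look of a plot, and does not say that inspection is blind to allocation.

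**The concern.** Three features of the rule do not suit a primary analysis.

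1. **It checks the wrong object.** A linear mixed model makes its normality assumption about residuals and random effects. The raw variables can look non-normal while the model is adequate.
2. **It can change what is estimated.** A difference in change on a transformed scale is a different comparison from a difference in change in points. A rank test gives a p-value without the planned mean difference. In either case the result cannot be set directly against the 10 points used to size the trial.
3. **It is triggered by eye.** Two competent analysts could look at the same histogram and report different primary analyses. Readers could not tell from the protocol which one should have been reported.

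At stake is whether the trial has a single primary analysis, fixed in advance, on the scale on which it was designed.

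**Working it through.** **1. The plan's own figure, and the scale it needs.** Inputs from *Sample size calculation* and *Statistical methods and analysis*: difference 10 points, SD 12.5, two-sided alpha 0.05, power 80%.

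n per arm = 2 × (1.960 + 0.842)² × (12.5/10)² = 2 × 7.85 × 1.5625 ≈ 24.5, so 25.

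The stated 25 per arm is reproduced. Power at 25 per arm is 0.807 by the normal approximation and 0.792 by the noncentral t. This calculation is for a difference in means in FSMC points. It does not describe a transformed outcome or a rank test.

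**2. What the rule permits for the primary outcome.**

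| Path | Analysis | Estimates the mean difference in points? |
|---|---|---|
| Plot judged acceptable | Mixed model on FSMC points | Yes |
| Plot judged poor, transformation judged to help | Mixed model on an unnamed scale | No |
| Still judged poor | Unnamed non-parametric test | No; a p-value only, unless an estimate is added |

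To illustrate the second row, take a log transformation (my choice; the protocol names none). A fall from 60 to 50 and a fall from 75 to 65 are both 10 points. On the log scale they are ln(60/50) = 0.182 and ln(75/65) = 0.143, so equal changes in points are no longer equal.

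**3. Cost in type I error.** Simulation with 25 per arm, SD 12.5 and no treatment effect; 15,000 runs per case, Monte Carlo standard error about 0.002. The distributions are assumed. A Shapiro-Wilk test at 5% stands in for the visual check.

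| Data | Fixed t-test | Fixed Wilcoxon | Mechanical switch | Smaller p always taken | Switch triggered |
|---|---|---|---|---|---|
| Normal | 0.052 | 0.049 | 0.053 | 0.061 | 5% |
| Gamma(2) skew | 0.048 | 0.048 | 0.052 | 0.063 | 92% |
| t(4) tails | 0.048 | 0.047 | 0.052 | 0.063 | 46% |

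The mechanical switch costs almost nothing. The worst case adds about one percentage point.

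**4. Whether the switch is needed.** With a 10-point shift (4,000 runs per case) the fixed t-test had power 0.80 in all three cases. It also kept its type I error, so validity at this sample size does not depend on switching.

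**5. Raw baseline against change.** *Eligibility criteria* requires "Presence of moderate to severe fatigue, defined as a Fatigue Scale for Motor and Cognitive Functions (FSMC) score" of at least 53, which truncates baseline FSMC. Assume a latent normal score with SD 12.5 and mean 60 to 75, cut at 53, n = 50, 2,000 draws. Repeated runs gave:

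- Raw baseline: skewness about 0.7 (mean 60) falling to about 0.25 (mean 75); Shapiro-Wilk rejection about 75% falling to about 10%.
- Change score, with an assumed baseline to follow-up correlation of 0.5 or 0.7: mean skewness -0.04 to -0.01; rejection 4 to 6%, the nominal rate.

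With one baseline, one follow-up and complete data, the group-by-time term of the mixed model is the difference in mean change. The quantity that bears on the treatment contrast is therefore hardly touched by the eligibility cut, while a plot of raw baseline scores may look clearly skewed.

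**The case against.** The strongest defence is that the normality sentences are a general preamble for a long list of very different outcomes (spectroscopy, motor evoked potentials, timed tests, diaries), for several of which transformation is reasonable, and that the primary outcome then gets its own named model. The inspection also comes before analysis and in a fixed order, so it is not a licence to choose by p-value. Which transformation and which rank test to use are details that an unseen SAP may settle. A rank test can also gain power: in the simulations with a 10-point shift, Wilcoxon reached about 0.88 under skewed or heavy-tailed data against 0.80 for the t-test, though 0.77 against 0.80 under normal data.

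Much of this stands. The missing names of transformation and test are not the complaint, and the rule is sensible for some secondary and exploratory outcomes. But its stated scope is all variables, and the primary outcome is not carved out. A SAP that fixed the primary analysis would depart from this text, so the wording needs attention either way. The possible power gain depends on the distribution and comes with a test that does not estimate the planned quantity.

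Three stronger readings are tempting and are not supported.

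- *Type I error is uncontrolled.* The simulated inflation is small, even in the worst case.
- *The cut at 53 makes a switch likely.* The high rejection rates apply to raw baseline scores only and come from a formal test that the protocol does not use. They also take 12.5 as the SD before truncation; after the cut the simulated baseline SD is only about 8.8 to 11.4.
- *The trial could no longer report points.* Nothing forbids giving the difference in points beside a rank test, and a Hodges-Lehmann shift with its interval would be in FSMC points. Neither is planned.

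**Conclusion.** The point holds as one of prespecification and interpretability. As written, the rule allows three primary analyses, chosen by a visual look at raw variables, and two of them do not estimate the mean difference in points on which the trial is defined and sized.

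The effect on type I error is slight: about 0.052 to 0.053 with a mechanical switch and 0.061 to 0.063 if the smaller p-value were always taken, against a nominal 0.05. These figures rest on assumed distributions, on a t-test in place of the mixed model, on Wilcoxon as the fallback, and on a formal test in place of the visual check. They do not cover the transformation step. How often a visual check would trigger a switch cannot be worked out from the document.

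This should be corrected, but it does not undermine the design.

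**What to change.** Reword the two normality sentences before unblinding so that:

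- the primary outcome is expressly exempt from transformation and from the non-parametric fallback;
- the primary analysis is the linear mixed model already named, on untransformed FSMC points, reported as the between-group difference in change with a 95% CI whatever the histograms show;
- diagnostics are made on model residuals, in particular those for within-person change, and not on raw variables;
- if residuals look poor, the primary estimate stays and a bootstrap interval, a permutation p-value or a rank analysis is added as sensitivity only;
- transformations are limited to named outcomes where skew is expected, such as timed tests and motor evoked potential amplitudes.

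The cost is a short text change. The sample size stays at 25 evaluable per arm, with power of 0.79 (t) to 0.81 (normal approximation) for 10 points at SD 12.5.
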